## Abstract

**Introduction:**

Focal therapy may reduce the toxicity of current radical treatments while maintaining the oncological benefit. Irreversible electroporation (IRE) has been proposed to be tissue selective and so might have favourable characteristics compared to the currently used prostate ablative technologies. The aim of this trial is to determine the adverse events, genito-urinary side effects and early histological outcomes of focal IRE in men with localised prostate cancer.

**Methods:**

This is a single centre prospective development (stage 2a) study following the IDEAL recommendations for evaluating new surgical procedures. Twenty men who have MRI-visible disease localised in the anterior part of the prostate will be recruited. The sample size permits a precision estimate around key functional outcomes. Inclusion criteria include PSA ≤ 15 ng/ml, Gleason score ≤ 4 + 3, stage T2N0M0 and absence of clinically significant disease outside the treatment area. Treatment delivery will be changed in an adaptive iterative manner so as to allow optimisation of the IRE protocol. After focal IRE, men will be followed during 12 months using validated patient reported outcome measures (IPSS, IIEF-15, UCLA-EPIC, EQ-5D, FACT-P, MAX-PC). Early disease control will be evaluated by mpMRI and targeted transperineal biopsy of the treated area at 6 months.

**Discussion:**

The NEAT trial will assess the early functional and disease control outcome of focal IRE using an adaptive design. Our protocol can provide guidance for designing an adaptive trial to assess new surgical technologies in the challenging landscape of health technology assessment in prostate cancer treatment.

## Introduction

1

Recent evidence from large randomised controlled trials (RCTs) in prostate cancer has challenged the current diagnostic and treatment pathway of the disease [1], [2]. This is due to an unfavourable benefit/risk ratio. This is because of two reasons. First, many men are diagnosed with indolent prostate cancer which do not impact on his quality of life or life expectancy [3], [4]. Second, when treatment is given, it is applied in a radical whole-gland manner (using surgery or radiotherapy) which causes collateral tissue damage and side effects. In summary, erectile dysfunction, urinary incontinence and bowel toxicity occur in about 40–95%, 10–20% and 5–35% of men undergoing radical therapy, respectively [5].

As a result, one strategy that has been proposed to mitigate the harms of the current pathway is focal therapy. This involves targeting therapy to the area of the prostate harbouring clinically significant disease (cancer that is not indolent and requires treatment), while sparing the rest of the gland. Indeed, by preserving prostatic tissue and the important structures surrounding the prostate — such as external urinary sphincter, neurovascular bundles, bladder neck, and rectum — the toxicity profile decreases significantly. A recent systematic review has shown that various sources of energy have been used for focal therapy [6]. Overall, erectile dysfunction, urinary incontinence and bowel toxicity were lower and ranged from 0 to 46%, 0 to 5% and 0 to 33%, respectively [6]. Cancer-control outcomes demonstrated residual cancer in 4–50% of men having a biopsy after treatment, although only 0–17% of residual disease was deemed clinically significant [6].

Currently, most of the energy sources used in a focal manner utilise a thermal effect to destroy prostatic tissue: cryotherapy uses temperatures below − 40 °C and high-intensity focused ultrasound therapy (HIFU) use temperatures above + 60 °C [6], [7]. Thermal tissue destruction may have some drawbacks. First, it is non-selective towards the different structures (nerves, stroma, vasculature, glands) of the prostate and collateral damage could still occur. Second, especially with high temperatures, the heat-sink effect of intra- and extra-prostatic vessels (which can dissipate the energy) can lead to under-treatment. Third, the precision required to treat an area of prostate to within millimetre accuracy may be lacking. New technologies in the field might combine better cancer control outcomes with enhanced tissue preservation.

Irreversible electroporation (IRE) is a promising new technology. By using low voltage direct electric current, IRE permanently damages the cell membrane, and leads to cell death with no thermal effect [8]. IRE has been used for the treatment of localised and metastatic tumours in other solid organ malignancies such as kidney, liver, pancreas and lung [9]. It has some potential advantages that might lend itself to focal therapy in prostate cancer. First, the tissue outside the electrical field is theoretically not compromised since there is no effect in those areas [8]. Second, the treatment has shown tissue-selectivity in pre-clinical studies, so that collagenous structures — such as vessels, nerves and the urethra — seem not to be affected [8], [10], [11].

As a result, we hypothesised that IRE would lead to low rate of side-effects when applied in a focal manner to men with clinically significant localised prostate cancer. To date, IRE has been used only in one proof of concept study with no intention to treat [12]. As a consequence, we followed the IDEAL guidelines for evaluating surgical innovation which recommends stages of evaluation and is mirrored upon the UK Medical Research Council's (MRC) Guidelines of evaluation complex interventions [13], [14].

The optimal trial design for ablative therapies has been debated and discussed in detail by numerous consensus groups of clinicians and methodologists [15], [16], [17]. The FDA in the US has also recently held a panel discussion in 2013 to look into this area [18]. The key problem has been in deciding on a trial design that shows benefit to patients. While side-effects could be measured in the short-term, disease control in a cancer which has a long natural history, is difficult to determine objectively. Our NEAT protocol, we believe, provides an exemplar of an adaptive design that would potentially answer the question about whether there is benefit in terms of reduced side-effects as well as provide robust data on the disease control outcomes in the short and medium term so that novel therapies can be approved in a timely manner to benefit men with prostate cancer.

## NEAT protocol

2

### Study management

2.1

NEAT is an investigator led single arm interventional adaptive trial compliant to the MRC guidelines for evaluating complex procedures, and to stage 2a (prospective development study) according to the IDEAL guidelines. Investigators from University College London (UCL) designed the protocol, considering feedback from the National Cancer Research Institute (UK) Prostate Clinical Studies Group as well as from patient representatives. The study is sponsored by UCL, and will be run at the University College London Hospital. The Joint Research Office of the local Research & Development unit is responsible for monitoring patients' safety and adherence to good clinical practice. The trial steering committee (TSC) is composed of an independent chair, the co-principal investigators, the study coordinators, a patient representative, two experts in the field and the study statistician. The independent data monitoring committee (IDMC) includes an independent chair expert in the field of prostate cancer therapy, a trial unit manager and a senior statistician (all of whom are independent of the study). This trial is registered in the clinicaltrials.gov database (NCT01726894).

### Study population eligibility

2.2

Men with histologically proven MRI-visible prostate cancer localised in the anterior part of the prostate. Therefore, only men with disease in the transition area, the anterior fibromuscular stroma or the peripheral zone of the prostate located in front of the urethra will be considered eligible. Presence of clinically significant disease outside the treated area represents an exclusion criteria, but insignificant disease left untreated is acceptable. A complete list of the eligibility criteria is given in Table 1.

**Table 1 t0005:** Inclusion and exclusion criteria for the NEAT trial.

*Inclusion criteria*
• Histologically proven prostate cancer, Gleason score ≤ 7.
• An anterior visible lesion on mpMRI, that is accessible to Irreversible Electroporation.
• Transperineal prostate biopsies (template mapping and/or zonal and targeted) correlating with clinically significant lesion in the area of the MR-visible lesion.
• Absence of clinically significant histological disease outside of the planned treatment zone.
• Stage radiological T1-T3aN0M0 disease, as determined by local guidelines.
• Serum PSA ≤ 15 ng/ml.
• Age ≥ 40 years and life expectancy of ≥ 10 years.
• Signed informed consent by patient.
• An understanding of the English language sufficient to understand written and verbal information about the trial and consent process.

*Exclusion criteria*
• Men who have had previous radiation therapy to the pelvis.
• Men who have had androgen suppression/hormone treatment within the previous 12 months for their prostate cancer.
• Men with evidence of metastatic disease or nodal disease outside the prostate on bone scan or cross-sectional imaging.
• Men with a non-visible tumour on mpMRI.
• Men with an inability to tolerate a transrectal ultrasound.
• Men with latex allergies.
• Men who have undergone prior significant rectal surgery preventing insertion of the TRUS probe (decided on the type of surgery in individual cases).
• Men who have had previous NANOKNIFE, HIFU, cryosurgery, thermal or microwave therapy to the prostate.
• Men who have undergone a Transurethral Resection of the Prostate (TURP) for symptomatic lower urinary tract symptoms within the prior 6 months. These patients may be included within the trial if deferred from consent and screening until at least 6 months following the TURP.
• Men not fit for major surgery as assessed by a consultant anaesthetist.
• Men unable to have pelvic MRI scanning (severe claustrophobia, permanent cardiac pacemaker, metallic implant etc likely to contribute significant artefact to images).
• Presence of metal implants/stents in the urethra.
• Men with renal impairment with a GFR of < 35 ml/min (unable to tolerate Gadolinium dynamic contrast enhanced MRI).

In this study, we use a definition specifically derived for transperineal biopsies, as those definitions based on transrectal biopsies have no proven validity in biopsies taken transperineally. Our definition is based on the presence of any positive core with primary or secondary Gleason pattern ≥ 4 (i.e., 3 + 4 or 4 + 3), and/or a maximum cancer core length ≥ 4 mm. Insignificant disease is defined as opposite as Gleason 3 + 3 with maximum cancer core length of 3 mm or less.

### Trial design

2.3

The trial flow and the visit schedule are displayed in Fig. 1, Fig. 2, respectively.

**Fig. 1 f0005:**
[figure not shown]
Trial flow.

**Fig. 2 f0010:**
[figure not shown]
Single visit schedule throughout the trial. Patient in the embedded qualitative study will have visits 4, 6 and 7 carried out in an alternative electronic manner, as shown in the table and legends.

#### Trial entry

2.3.1

It is of key importance to well select men who are likely to benefit from focal treatment in which significant disease is localised in only one part of the gland. To avoid the possibility of leaving clinically significant cancer untreated, all patients undergone state-of-the-art accurate imaging and tissue sampling. Only men in which imaging and histology are concordant in localising disease in the anterior part of the prostate were eligible.

A mpMRI will be performed in a 1.5 Tesla or 3 Tesla scanner and a pelvic phased array receiver with a pelvic coil using a standardized protocol as described elsewhere [19]. The protocol includes T2-weighted, dynamic contrast enhanced and diffusion-weighted images. The sequences used and the reporting method will follow those laid down by the European society of uro-radiology [20]. The images will be evaluated and reported by experienced radiologists who will score the likelihood of significant disease in a zonal fashion following international guidelines [21]. MpMRI of the prostate using this protocol has been shown to be able to rule out clinically significant disease with a negative predictive value at 90–95% in centres of excellence when compared to accurate reference tests [22], [23].

All men will need also to undergo accurate biopsy using the transperineal route. Both template prostate mapping with 5 mm sampling density and zonal template biopsy with targeted biopsy of MR-derived targets will be accepted. These tests have been shown to be comparable in terms of diagnostic accuracy and both yield a NPV again around 90–95% [24], [25], [26], [27].

While no single test can definitely rule out clinically significant disease, the combination of accurate imaging and histology minimises (although not eliminates) the possible miss-classification of untreated areas.

All men with a new diagnosis of prostate cancer are counseled about all standard radical therapeutic options. Those meeting the inclusion criteria for the NEAT trial are offered a patient information sheet, and to attend a screening and consent visit if interested. The consent, medical history, physical examination, and blood tests including a PSA test are collected. At baseline, a number of validated patient reported outcome measures (PROMs) are completed: International Prostate Symptom Score (IPSS) and IPSS Quality of Life (IPSS-QoL), 15-Item International Index of Erectile Function (IIEF-15), UCLA Expanded Prostate Cancer Index Composite (EPIC) urinary and bowel domains, EQ-5D Health related Quality-of-life, Functional Assessment of Cancer Therapy for Prostate (FACT-P) and Memorial Anxiety Scale for Prostate Cancer (MAX-PC) [28], [29], [30]. Patients are also asked whether they want to participate to an optional embedded qualitative study aiming to assess patients' satisfaction with alternative electronic forms of follow-up.

#### Focal irreversible electroporation

2.3.2

Under general anaesthesia and deep muscle paralysis, a suprapubic catheter or a urethral catheter, in case of contraindication to a suprapubic catheter, are inserted. The 19 G electrode-needles are inserted via a transperineal approach under transrectal ultrasound (TRUS) guidance using a brachytherapy grid. The electrical field in IRE is created by positioning electrodes to the margins of the tumour (Nanoknife™, AngioDynamics, New York, USA). The number of electrodes used is dependent on the size and the shape of the lesion to treat (Fig. 3). Usually, four electrodes are required to cover a discrete lesion within the prostate, although one additional electrode may be needed in larger lesions. The device will be set to deliver 90 pulses with a pulse length at 70 μs in order to achieve an electrical field between 20 and 40 A. This current has been shown to cause complete ablation in the target area without causing heating effect, which in turn is possible when the current is higher [31].

**Fig. 3 f0015:**
[figure not shown]
This a representative diagram of the treatment planning for irreversible electroporation of the prostate. Left and right images represent an axial and sagittal views of a TRUS, respectively. The electrodes are positioned around the lesion to treat (left image), highlighted as a red spot. A given active length exposure (blue arrow in the right image) is determined according to the longitudinal dimension of the lesion.

In this study, to allow precise placement of the electrode-needles, a MR/TRUS fusion device is used. Various studies have previously shown that integrating mpMRI images to real-time TRUS images can be beneficial to better target intra-prostatic tumours for biopsy and one previous study has shown that fusion is feasible with HIFU focal therapy [32], [33], [34]. In the NEAT trial we will use a high accuracy MR/TRUS fusion device (SmartTarget) that by non-rigid registration compensates for the distortion of the prostate [35], [36]. This fusion device is currently under development and commercialisation at UCL. Since this is a pilot study, and the accuracy of this software is yet to be defined for IRE focal therapy, the surgeon is free to accept or reject the treatment planning calculated by the software.

Once the electrodes have been positioned, the surgeon will measure the distances between the electrodes and will select the electrodes' active length according to the cranio-caudal length of the target area. Based on these two measurements which are manually entered in the device, the Nanoknife software calculates the voltage necessary to obtain the optimal electrical field (20–40 A). After the first 10 pulses have been delivered, the actual electrical field in the prostatic tissue is verified. If the electrical field is in the optimal range, then the remaining 80 pulses are delivered; otherwise, the voltage is modified as required.

The focal IRE treatment is planned as a day-case procedure. Men arrive in the morning of the procedure, and are usually discharged in the afternoon or in the evening. Catheter withdrawal is scheduled between 3 and 10 days at the same time of the early contrast MRI scan. Patients are prescribed pain killers, antibiotics and laxatives for one week after the procedure.

##### Therapy escalation and rationale

2.3.2.1

Only men with MR-visible anterior disease will be treated. At this early stage of evaluation of this treatment, targeting the anterior part of the prostate is the safest approach since it is away from the rectum. As a consequence, rectal toxicity, and particularly the risk of recto-urethral fistula are minimised since no previous clinical study has accurately shown the extent of ablation that can be achieved with IRE.

In this prospective development study, we have incorporated a ‘dose-escalation or dose optimisation’ protocol based on target volume. Indeed, using a fixed algorithm including fixed pulse length and number of pulses, the delivered energy is mainly determined by the needle active length and by the needle distances, which in turn are both derived by the target volume. We are going to stratify the first nine patients into three groups of three patients each based on a maximum target volume. The ablation volume in millilitres has been calculated with respect to an average prostate volume, which corresponds to 40 ml. In the first group, a maximum of 4 ml ablation or target volume representing maximum 15% of the prostate volume is admitted. This represents the minimum amount of tissue that is estimated to be possible to ablate in focal therapy. The limit will be increased to 15 ml ablation or 40% prostate volume, and to 20 ml ablation or 50% prostate volume, for the second and third group, respectively. The upper threshold corresponds to the maximum amount of tissue it would be possible to treat in each subgroup of patients and not a target to achieve. In the remaining 11 patients, the upper threshold set at 20 ml ablation or 50% prostate volume will be respected.

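### The group 1 volume cap pairs 4 ml with 15%, but at the stated 40 ml reference prostate 4 ml is 10% and 15% is 6 ml

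*Protocol article*

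**What the plan says.** The passage is in the protocol article, section 2.3.2.1 (Therapy escalation and rationale). Target volume serves as the dose variable, and the early patients are treated under rising caps: "We are going to stratify the first nine patients into three groups of three patients each based on a maximum target volume".

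The basis for the millilitre figures is given: "The ablation volume in millilitres has been calculated with respect to an average prostate volume, which corresponds to 40 ml".

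The group 1 cap follows directly: "a maximum of 4 ml ablation or target volume representing maximum 15% of the prostate volume is admitted". The article then comments on that amount: "This represents the minimum amount of tissue that is estimated to be possible to ablate in focal therapy".

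For groups 2 and 3: "The limit will be increased to 15 ml ablation or 40% prostate volume, and to 20 ml ablation or 50% prostate volume". For everyone after that: "In the remaining 11 patients, the upper threshold set at 20 ml ablation or 50% prostate volume will be respected".

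The caps are ceilings. Each is described as the "maximum amount of tissue it would be possible to treat in each subgroup of patients and not a target to achieve".

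**The concern.** If the millilitre caps were derived from a 40 ml gland, each cap and its percentage should convert into one another at 40 ml. Group 1 does not.

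Group 1 is the cautious opening step of a treatment for which, by the article's own account in the same section, no earlier clinical study had accurately established how much tissue is ablated. The ceiling for those three men should have one meaning. As printed, a reader applying it to a 40 ml gland could arrive at 4 ml or 6 ml.

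The group 1 cap has one further use. Under section 2.3.5 (Stopping rules), a recto-urethral fistula is expected to send the target volume back to the previous maximum. If that happened in group 2, the previous maximum would be the group 1 cap.

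**Working it through.** **Inputs, all from section 2.3.2.1.** Reference prostate V = 40 ml. Printed caps: group 1, 4 ml and 15%; group 2, 15 ml and 40%; group 3 and the remaining 11 men, 20 ml and 50%.

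**Formulas.** Volume implied by the percentage = percentage × V. Percentage implied by the volume = ml ÷ V. Gland size at which the two agree = ml ÷ percentage.

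| Group | Printed pair | Percentage × 40 ml | ml ÷ 40 ml | Gland where the pair agrees |
|---|---|---|---|---|
| 1 | 4 ml, 15% | 0.15 × 40 = 6 ml | 4/40 = 10% | 4/0.15 = 26.7 ml |
| 2 | 15 ml, 40% | 0.40 × 40 = 16 ml | 15/40 = 37.5% | 15/0.40 = 37.5 ml |
| 3 and remaining 11 | 20 ml, 50% | 0.50 × 40 = 20 ml | 20/40 = 50% | 20/0.50 = 40 ml |

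**Does the plan's own basis reproduce its figures?**
- Group 3 and the remaining 11 men: yes, exactly.
- Group 2: yes, if 37.5% was rounded to the nearest 5%, which gives 40%. The gap is 16 − 15 = 1 ml, or 1/15 = 6.7% of the printed cap. The article states no rounding rule, so this is an inference.
- Group 1: no. 4/40 is exactly 10%, so rounding cannot produce 15%. The gap is 6 − 4 = 2 ml, or 2/4 = 50% of the printed cap. The pair agrees only in a 26.7 ml gland, a size the article does not mention.

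**What a matched pair would and would not settle.** A corrected pair agrees at 40 ml only. The article gives no range of gland sizes, so 20, 30, 60 and 80 ml are assumed here for illustration. The group 2 limits would be 15 ml by volume against 40% = 8, 12, 24 and 32 ml. The group 3 limits would be 20 ml against 50% = 10, 15, 30 and 40 ml. Correcting group 1 therefore does not fix the ceiling for an individual man unless it is also known which limit governs.

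**The two candidate corrections, if the lower limit governs.** In an assumed 30 ml gland:
- 4 ml/10% gives min(4, 3) = 3 ml. It falls below 4 ml in every gland under 40 ml.
- 6 ml/15% gives min(6, 4.5) = 4.5 ml. It falls below 4 ml only in glands under 4/0.15 = 26.7 ml.

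**The case against.** The strongest reply is that there may be no error. The group 1 sentence is worded differently from the later ones and uses the word maximum twice. It can be read as a 4 ml cap on the ablation or target volume, taken as two names for one quantity, with 15% as an outer bound on the share of the gland it may take up. On that reading 4 ml need not equal 15%. It satisfies the bound at 40 ml and in any gland of 26.7 ml or more. At 40 ml the millilitre cap is at or below the percentage cap in all three groups (10%, 37.5% and 50% against 15%, 40% and 50%), which fits the same reading, and group 2 is not an exact match either.

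This stands as a possibility and is the reason confidence is medium and not high. It is less likely than the paired reading for three reasons. The text says the millilitre volumes were derived from the 40 ml gland. The next sentence raises a single limit and gives it each time as a volume or a percentage: "The limit will be increased to 15 ml ablation or 40% prostate volume, and to 20 ml ablation or 50% prostate volume". The later pairs then convert at 40 ml, exactly or to rounding.

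A reader might seek further proof in the size of the steps: from group 1 to group 2 the cap rises 15/4 = 3.75-fold in millilitres but 40/15 = 2.67-fold in percentage. This is not independent evidence. It assumes that the two scales must move together, which is the question in dispute, and the step from group 2 to group 3 also differs (20/15 = 1.33 against 50/40 = 1.25).

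The reply that the practical effect is small also stands. The cap is not a target, the disease is anterior and away from the rectum, and even 6 ml is far below the 15 ml allowed to the next three men.

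**Conclusion.** The group 1 pair does not follow from the 40 ml basis stated for it. Unless 15% was intended only as an outer bound, the first-step ceiling at the reference gland can be read as 4 ml or 6 ml. This is a minor point, held with medium confidence. It rests on two assumptions: that volume and percentage are paired expressions of one limit, and that group 2 was rounded.

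The size is 2 ml in 3 of 20 men. The document does not show which figure is wrong.

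Three stronger inferences are not supported:
- That the first men could be seriously over-treated. The larger reading is 6 ml, and it is a ceiling.
- That the fistula step-back is undermined. A return from 15 ml to 4 ml or to 6 ml is a large reduction either way, and its direction is unchanged.
- That the statistics are affected. The sample size and outcome definitions in section 2.3.7 do not use the caps.

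The article's silence on which limit governs is not counted as a separate fault, since a condensed article may leave that to the full protocol. It matters here because a correction to group 1 would be incomplete without it.

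**What to change.** The clinical team should correct the group 1 pair to 4 ml/10% or 6 ml/15%, whichever was intended. They should also add one sentence, applying to all groups, saying which limit governs when the millilitre and percentage caps differ in a man's actual gland. If 15% really was an outer bound for group 1, that sentence should say so.

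The cost is one number and one sentence, with no extra patients, procedures or analyses. Each option has a small downside. If the lower limit governs, 4 ml/10% allows less than 4 ml in glands under 40 ml, which sits against the statement that the group 1 amount "This represents the minimum amount of tissue that is estimated to be possible to ablate in focal therapy". Choosing 6 ml/15% largely avoids that, but makes the first step slightly less cautious at the reference gland.
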